### Secondary outcomes

Secondary outcome will include the proportion of patients that achieve remission and response to each treatment at the end of each phase of the study, according to improvement on the rating scales (Hamilton Depression Scale; Montgomery–Åsberg Depression Rating Scale; Young Mania Rating Scale) and in CGI-BP-M [31]. The CGI-BP-M is a clinician rating scale modified for BD for assessing treatment response and consists of three subscales evaluating severity of mania, depression and global disease symptoms.

Other outcome parameters include safety and tolerability, quality of life and social adjustment, and cognitive impairment. These parameters will be evaluated by comparing the endpoint measures for each phase with baseline values. Safety and tolerability were determined according to the clinical evaluation of adverse effects and score on the UKU side-effect rating scale [32]. The UKU comprises a 48-item clinician rated scale evaluating side effects in psychic, neurologic, autonomic and other domains. Quality of life and social adjustment were measured with the WHOQoL-BREF [33] and the Social Adjustment Scale [34]. These instruments were previously translated and validated into Portuguese [35,36]. The WHO-QOL-BREF is a 26-item self-report scale comprising four domains: physical, psychological, social, and environmental. The Social Adjustment Scale is a 54-question self-report instrument that measures instrumental and expressive role performance over the previous 2 weeks. Cognitive impairment was measured neuropsychological tests (Wisconsin Card Sorting Test, Stroop Color Word Test [37], Wechsler Abbreviated Scale of Intelligence [38], Trail Making Test [37] and others), for which versions are available in Portuguese. All investigators received appropriate training, and inter-rater reliability is periodically assessed.

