**Discussion:**

The ARIQUELI study is currently in progress, with patients undergoing acute treatment (phase I), potentiation (phase II) and maintenance (phase III). The study will be extended until January 2015. Trials comparing lithium and aripiprazole with potentiate treatment in young BD I nonresponders to quetiapine in monotherapy can provide relevant information on the safety of these drugs in clinical practice. Long-term treatment is an issue of great importance and should be evaluated further through more in-depth studies given that BD is a chronic disease.

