### Sample size and randomization

Sample size was calculated by comparing the mean difference in Clinical Global Impression for Bipolar Disorders (CGI-BP-M) scores between baseline and endpoint for the two groups. Comparison using Student's *t* test showed that a sample of 50 patients (25 in each group) attains an 80% power (at 5% significance level) for detecting a difference of 0.8 standard deviations, considered a large effect size [27]. Owing to the exploratory nature of this study and the difficulties regarding compliance in long-term trials, this was deemed an acceptable value [27].

The random allocation sequence was computer generated by a biostatistician. Patients were enrolled by clinicians who have their code revealed by the research monitor when assigned to interventions. Blinding of outcome assessors is ensured by keeping their evaluations independent from those of the clinicians.

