### Study phases

Patients will be followed up for 8 weeks in phase I (acute treatment), 8 weeks in phase II (potentiation treatment) and shall continue in phase III (maintenance) until study endpoint at 2 years. Scale raters will be blind to the treatment. Only patients that respond will continue to phase 3, with response determined according to the initial symptoms score in phase I. Patients in phase III using quetiapine alone that present a new episode of any polarity, as detected on two consecutive visits, will start phase II (potentiation treatment). Patients that show no response after phase II will be dropped from the study.

The definition of clinical course is defined as follows: no response, reduction ≤25% in severity of symptoms; partial response, improvement of 26 to 49% in symptoms; response, reduction ≥50% in severity of symptoms; remission, minimal or no symptoms for at least 1 week, Hamilton Depression Scale ≤7 and Young Mania Rating Scale ≤9; sustained remission, ≥8 weeks of remission; relapse/recurrence, return of the signs and symptoms for the syndrome as per criteria; and worsening, return of symptoms at subsyndromal level [28-30].

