### Planned analyses

The primary analysis will entail evaluation of mean scores on the CGI-BP-M between baseline and endpoint in both groups. In addition, differences shall be evaluated by comparing the two treatment groups according to the total number of patients in full remission at the study endpoint and the reason for and timing of drop out. Continuous data will be represented as mean and standard deviation whereas categorical variables will be described by a table of frequencies. The results of all statistical comparisons of the treatment groups will be expressed as two-sided *P* values rounded to three decimal places. The criterion for statistical significance in all comparisons will be *P* ≤0.05.

Continuous variables will be compared using repeated-measures of analysis of variance, with the treatment group and study phase as factors. Rates of response, remission and dropouts will be compared between the two groups using Pearson's chi-square test for categorical data. Dichotomous measures will also be compared using odds ratios and 95% confidence limits.

The correlation of clinical issues, quality of life, social adjustment and cognitive impairment will be evaluated by Pearson's correlation.

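### Comparing safety at the end of each phase with baseline misses transient side effects, can lose early stoppers' UKU scores, and in phase III rests on responders only

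*Protocol article*

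**What the plan says.** Under Secondary outcomes, safety and tolerability are grouped with quality of life, social adjustment and cognitive impairment, and one rule serves all of them: "These parameters will be evaluated by comparing the endpoint measures for each phase with baseline values". The measures are then named: "Safety and tolerability were determined according to the clinical evaluation of adverse effects and score on the UKU side-effect rating scale".

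Under Planned analyses, the model for scores is given: "Continuous variables will be compared using repeated-measures of analysis of variance, with the treatment group and study phase as factors". Two further between-arm comparisons are relevant. One is "the reason for and timing of drop out". The other is the test of rates: "Rates of response, remission and dropouts will be compared between the two groups using Pearson's chi-square test for categorical data". Odds ratios with 95% limits are added for dichotomous measures. Adverse effects are not among the rates listed.

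Under Study phases, "Only patients that respond will continue to phase 3", and patients without response after phase II leave the study. The abstract's discussion says that trials of this kind "can provide relevant information on the safety of these drugs in clinical practice".

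**The concern.** The rule handles side effects as if they were an efficacy score, with one value at the start and one at the end of a phase. Three kinds of information can be lost.

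- **Transient effects.** The Interventions section adjusts both add-ons for tolerability and permits biperiden and lorazepam. An effect that was managed or had passed before the end-of-phase rating does not show in it. Phase III is long (until the 2-year endpoint under Study phases, 12 months in the abstract), so a single closing rating says little about the exposure.
- **Early stoppers.** The Primary outcomes section places the endpoint at the end of each phase. If the same meaning applies to the UKU, a patient who stops for intolerance has no endpoint score. Repeated-measures analysis of variance in its classical form then leaves that patient out.
- **Selection.** By phase III, the add-on patients still rated are those who responded.

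Tolerability is part of the trial's full name, and the abstract offers the results as evidence on safety. If one add-on is stopped more often for side effects, the comparison among those who remain would understate the difference.

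**Working it through.** The documents give no adverse-effect or dropout rates, so all rates below are assumptions. The only expectation on record is a remark in the sample-size section, made to justify the effect size: "Owing to the exploratory nature of this study and the difficulties regarding compliance in long-term trials, this was deemed an acceptable value".

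**The plan's own figure, for context.** 25 per arm, 0.8 SD, two-sided 5%: power is 0.807 by the normal approximation and 0.791 by the noncentral t. The stated 80% is reproduced and not disputed.

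**Check 1: mean UKU score.** Assume scores are normal with SD 1, the less well-tolerated arm is worse by D, and the fraction d of each arm that stops consists of its highest scorers, who have no endpoint score. The mean of those remaining falls by φ(c)/(1−d), with c = Φ⁻¹(1−d). This fall is 0.109 at d = 5%, 0.195 at 10%, 0.350 at 20%, 0.497 at 30% and 0.644 at 40%. The observed difference is D, minus the fall in the worse arm, plus the fall in the other arm.

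| Stopping, better v worse arm | D = 0.3 | D = 0.5 | D = 0.8 |
|---|---|---|---|
| 10% v 10%, or 20% v 20% | 0.30 | 0.50 | 0.80 |
| 5% v 10% | 0.21 | 0.41 | 0.71 |
| 5% v 20% | 0.06 | 0.26 | 0.56 |
| 5% v 30% | −0.09 | 0.11 | 0.41 |
| 10% v 40% | −0.15 | 0.05 | 0.35 |

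For example, at D = 0.5 and 5% v 20%: 0.5 − 0.350 + 0.109 = 0.26. Equal stopping leaves no bias. Unequal stopping shrinks the difference. The sign changes only when a small true difference meets a gap in stopping of 25 to 30 points.

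**Check 2: proportion with a troublesome side effect.** Assume true rates of 40% v 16%, and that a fraction s of affected patients stops in both arms. The rate among those remaining is p(1−s)/(1−ps).

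| s | Stopped (ps) | Rate among those remaining | Risk difference | Odds ratio |
|---|---|---|---|---|
| 0 | 0% v 0% | 40% v 16% | 24.0 points | 3.5 |
| 0.5 | 20% v 8% | 25.0% v 8.7% | 16.3 points | 3.5 |
| 0.7 | 28% v 11.2% | 16.7% v 5.4% | 11.3 points | 3.5 |
| 0.9 | 36% v 14.4% | 6.3% v 1.9% | 4.4 points | 3.5 |

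The odds among those remaining are p(1−s)/(1−p), so a common s cancels from the ratio: (0.40/0.60)/(0.16/0.84) = 3.5 in every row. Only the absolute difference shrinks, and the worse arm still looks worse throughout.

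**Check 3: the planned dropout comparison as a safeguard.** With n = 25 per arm and p̄ the mean of the two rates, power = Φ{[|p₁−p₂| − 1.96√(2p̄(1−p̄)/n)] / √([p₁(1−p₁)+p₂(1−p₂)]/n)}. This gives 0.36 for 5% v 20%, 0.65 for 5% v 30%, 0.42 for 10% v 30% and 0.70 for 10% v 40%. For the stopping rates in check 2 it gives 0.23 (8% v 20%), 0.32 (11.2% v 28%) and 0.42 (14.4% v 36%).

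**The case against.** The strongest reply has four parts.

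- **Nothing in the text excludes early stoppers.** The article does not say how the endpoint is taken for someone who leaves, and a last available rating is possible. This stands: losing their UKU scores is a risk the wording leaves open, and it is not a stated rule. The kinder reading does not, however, recover effects that resolved before the last rating.
- **Stopping is already compared between arms**, by reason, timing and rate. This also stands, and a less well-tolerated add-on should leave a signal there. That signal is partial: the power in check 3 is modest, and the comparison returns neither transient effects nor leavers' scores.
- **The size depends on assumed rates and on the scale.** Planned analyses names odds ratios for dichotomous measures, and check 2 leaves the odds ratio unchanged. This stands, so shrinkage can be claimed only for the mean score or the risk difference.
- **Safety populations and adverse-event windows usually belong to the full protocol or analysis plan**, which are not shown. Their absence from an article is therefore no fault. The point here is different: the article does state a rule for safety, and that rule is a poor one.

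A reader might infer that the worse-tolerated add-on will look safer than the other. The documents do not support this. It would take unequal stopping, stoppers left out of the analysis, and the extreme combinations in check 1.

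**Conclusion.** The point holds in a limited form. As worded, the rule misses side effects that come and go within a phase, can leave out UKU scores of patients who stop for intolerance, and in phase III describes responders only. The first and third follow directly from the text. The second depends on how the endpoint is defined for a patient who stops.

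The expected direction is shrinkage of the mean UKU difference or the risk difference, and only if tolerability-related stopping is unequal between the arms. Under the assumptions shown, 0.5 SD reads as 0.41 to 0.05 SD, and 24 points read as 16.3 to 4.4 points. The lower ends are upper-bound scenarios for the bias. The odds ratio need not move if the same fraction of affected patients stops in both arms. This is a secondary outcome in a trial that calls itself exploratory. The rule should still be changed, because tolerability is one of the trial's declared questions and the remedy is cheap.

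**What to change.** Replace the safety part of the shared rule in Secondary outcomes with a separate between-arm comparison:

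1. Include all randomised patients who took at least one add-on dose.
2. Count adverse effects from the first add-on dose to last contact.
3. Compare the arms on the worst (or last available) UKU score after randomisation, fixing in advance which of the two is used. Only the worst score retains effects that had resolved by the last rating. Use the ratings already collected, plus one at the stopping visit where possible.
4. Report dropout due to adverse effects, already covered by the planned comparison of reasons, beside it as a named tolerability outcome.
5. Keep the end-of-phase UKU against baseline as description.

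The cost is a change of wording, an occasional extra rating at a stopping visit and slightly more analysis work. Reported side-effect rates will be somewhat higher than under the present rule. No treatment rule changes.

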### Planned analyses

The primary analysis will entail evaluation of mean scores on the CGI-BP-M between baseline and endpoint in both groups. In addition, differences shall be evaluated by comparing the two treatment groups according to the total number of patients in full remission at the study endpoint and the reason for and timing of drop out. Continuous data will be represented as mean and standard deviation whereas categorical variables will be described by a table of frequencies. The results of all statistical comparisons of the treatment groups will be expressed as two-sided *P* values rounded to three decimal places. The criterion for statistical significance in all comparisons will be *P* ≤0.05.

Continuous variables will be compared using repeated-measures of analysis of variance, with the treatment group and study phase as factors. Rates of response, remission and dropouts will be compared between the two groups using Pearson's chi-square test for categorical data. Dichotomous measures will also be compared using odds ratios and 95% confidence limits.

The correlation of clinical issues, quality of life, social adjustment and cognitive impairment will be evaluated by Pearson's correlation.

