### Interventions

After diagnostic assessments, the patients initiate treatment with quetiapine for 8 weeks as described above. For acute treatment, patients shall receive a starting dosage of 100 mg on day 1, to be increased by 100 mg/day to 300 mg on day 3. The 300 mg dose shall be subsequently adjusted until reaching the most effective dose according to clinical criteria. The patient dose shall be determined according to individual tolerability, and a maximum dose of 800 mg will be allowed for this study. Patients showing remission or >50% reduction in baseline scores on the Hamilton Depression Scale and the Young Mania Rating Scale shall proceed to the maintenance phase for a further 18 months. Patients showing score reductions <50% on the scales will be allocated to one of the arms of the augmentation phase. Group I will receive lithium at the standard dose: starting at 300 mg daily, the weekly dose will be adjusted according to blood serum level (between 0.5 and 0.8 mEq/l) according to efficacy and tolerability. Group II will receive aripiprazole: starting at 10 mg daily, the dose will be adjusted up to 15 mg daily according to efficacy and tolerability. The only concomitant medications permitted are lorazepam at doses of 0.5 to 4 mg/day and biperiden at 2 to 8 mg/day.

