### Primary outcomes

Primary outcome will consist of the evaluation of changes in mean scores on the CGI-BP-M between baseline and endpoint at the end of each phase of the study.

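### The stated CGI-BP-M analysis names no pre-randomisation score as a covariate, so an unbiased comparison of 25 per arm may lose precision that could be recovered at almost no cost

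*Protocol article*

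**What the plan says.** All places are in the Methods/Design part of the protocol article.

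- **Primary outcomes:** the outcome is "changes in mean scores on the CGI-BP-M between baseline and endpoint at the end of each phase of the study".
- **Sample size and randomization:** the trial was sized by "comparing the mean difference in Clinical Global Impression for Bipolar Disorders (CGI-BP-M) scores between baseline and endpoint for the two groups". The stated basis is a Student's t test with 25 per arm, 50 in all, for 80% power at the 5% level. The target is given only in standardised form, "for detecting a difference of 0.8 standard deviations, considered a large effect size".
- **Planned analyses:** "The primary analysis will entail evaluation of mean scores on the CGI-BP-M between baseline and endpoint in both groups". The model for continuous outcomes follows: "Continuous variables will be compared using repeated-measures of analysis of variance, with the treatment group and study phase as factors". Tests are two-sided at 0.05.
- **Interventions:** allocation comes after 8 weeks of quetiapine: "Patients showing score reductions <50% on the scales will be allocated to one of the arms of the augmentation phase".
- **Study phases:** phase III is open to responders only, and patients without response after phase II leave the study. A patient on quetiapine alone who has a new episode in phase III moves to phase II.

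No section names ANCOVA or any covariate. No section says whether the baseline of the CGI-BP-M change is the rating at entry or the rating at allocation.

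**The concern.** Patients are not randomised at entry. They are randomised after a first phase on quetiapine, and the primary outcome calls for CGI-BP-M at the end of each phase. For patients allocated at week 8, a rating close to randomisation therefore already exists. It probably predicts the later ratings to some degree, and no lithium-aripiprazole difference can be present in it.

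As written, an early score can enter the analysis in two ways: subtracted from the endpoint, or as one level of the repeated phase factor. Subtraction fixes the slope on the early score at 1, whatever the data show, and so carries more of its noise into the outcome than necessary unless the true slope is 1. With 25 per arm, a large target effect and acknowledged compliance problems over a long follow-up, the trial has little precision to spare.

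The second route raises a conditional concern. If ratings from before allocation are levels of the phase factor, the group main effect averages the arm difference over levels at which it must be zero.

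**Working it through.** **Inputs from the article.** n = 25 per arm; standardised difference 0.8, read as SDs of the change score because the sample size was set on change; two-sided alpha 0.05; Student's t test.

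**Assumed, because the article does not give them.** r, the correlation between the pre-randomisation and endpoint scores; k, the ratio of pre-randomisation SD to endpoint SD; 25 completers per arm.

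**1. The plan's own figure.** The normal approximation gives 25 per arm and 80.7% power. The exact noncentral t (48 df, noncentrality 0.8 × √(25/2) = 2.83) gives 79.1% at 25 per arm and 80.7% at 26. The stated 80% reproduces.

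**2. Variance with equal SDs (k = 1).** In units of the endpoint variance, the change score has variance 2(1 − r) and ANCOVA has 1 − r². Their ratio is (1 − r²) / [2(1 − r)] = (1 + r)/2.

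**3. Power with ANCOVA, k = 1.** The effective difference is 0.8 / √[(1 + r)/2 × (1 + 1/46)], on 47 df. The factor 1 + 1/46 allows for chance imbalance in the covariate.

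| r | Variance ratio | Effective difference | Power, ANCOVA | Power, change score |
|---|---|---|---|---|
| 0.2 | 0.60 | 1.022 | 94% | 79% |
| 0.5 | 0.75 | 0.914 | 89% | 79% |
| 0.7 | 0.85 | 0.858 | 84% | 79% |
| 0.9 | 0.95 | 0.812 | 80% | 79% |

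A simulation of 6,000 trials per value gave 88.5% at r = 0.5 and 85.0% at r = 0.7 for ANCOVA, and about 80% for the change score. Leaving the imbalance factor aside, ANCOVA has the power planned for 0.80 SD at a difference of 0.8 × √0.75 = 0.69 SD of change when r = 0.5.

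**4. Unequal SDs.** In general the variance ratio is (1 − r²) / (1 + k² − 2rk). It equals 1 when r = k, because the regression slope r/k is then 1 and subtraction is already the best adjustment. Power with ANCOVA, against 79% for the change score:

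| k | r = 0.2 | r = 0.5 | r = 0.7 |
|---|---|---|---|
| 0.8 | 90% | 83% | 79% |
| 0.7 | 87% | 80% | 78% |

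Values of k below 1 are plausible here. Entry requires minimum symptom scores, and only patients with less than 50% improvement are allocated, so the spread before randomisation may be restricted.

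**5. Conditional dilution.** Suppose that entry and the ends of phases I, II and III are all outcome levels, that the arms differ only at the last two, that every pair of ratings has correlation r, and that SDs are equal. The arm difference at those levels is D = 0.8 × √[2(1 − r)] endpoint SDs. The group main effect sees D/2, with an SD of √[(1 + 3r)/4] for the four-rating mean. Its power is 79%, 42% and 23% at r = 0.2, 0.5 and 0.7. The group-by-phase test (3 and 144 df) on the same data has 93% power, or 83% if the arms differ only at the end of phase III.

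**The case against.** The strongest case against has five parts.

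- **The article is a summary.** It lists two factors and excludes no covariate; an analysis plan that is not shown could add one. This stands as a limit: it cannot be said that the baseline score will never be used. But the article does state the model and its terms, and a covariate is not among them.
- **The dilution is not a stated feature of the plan.** A reader might infer that the primary test has as little as 23% to 42% power. The article does not support this. It says neither that ratings from before allocation are outcome levels nor that the group main effect is the test. The lithium and aripiprazole groups exist only after allocation, so the levels may be phases II and III alone. If earlier levels are included, the group-by-phase test is the natural one and avoids the dilution. Its weakness is that it is an omnibus test and gives no single arm difference.
- **The entry score is not stated to be the one subtracted.** A reader might infer this because the Interventions section measures response from baseline scores and the Study phases section uses the initial phase I score. Neither defines baseline for the CGI-BP-M change.
- **The gain depends on r and on the SDs.** This stands: with k = 0.7 and r of 0.5 to 0.7, nothing useful is gained.
- **Phase III will not hold 25 per arm,** because only responders continue. This also stands. The power figures illustrate a complete comparison and do not forecast the phase III result.

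**Conclusion.** The point holds as a matter of efficiency. The named terms are treatment group and phase, the outcome is a change from an undefined baseline, and no pre-randomisation CGI-BP-M score is used as a covariate. The comparison of randomised arms is not biased by this, and the sample size is not wrong.

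With equal SDs and 25 completers per arm, the power forgone is about 15 percentage points at r = 0.2, 10 at r = 0.5 and 5 at r = 0.7, and close to nothing at r = 0.9. It can also vanish when the pre-randomisation SD is well below the endpoint SD and r is about 0.5 to 0.7. Over the values examined, the worst result for ANCOVA was 78% against 79%, so there is little to lose and possibly much to gain. Dilution of a group main effect is a further risk only if ratings from before allocation are entered as phase levels and that term is the one tested; the wording leaves both open.

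**What to change.** In Planned analyses, replace the sentence on repeated-measures ANOVA, for CGI-BP-M, with the following specification:

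- **Outcome:** CGI-BP-M ratings made after randomisation only.
- **Model:** ANCOVA, or a mixed model with arm, phase and arm-by-phase, with the last CGI-BP-M rating before allocation as covariate.
- **Covariate defined for every route into randomisation:** the end-of-phase-I rating for patients allocated at week 8; the last rating recorded before allocation for patients who enter phase II after a relapse in phase III.
- **Reported result:** the adjusted lithium-aripiprazole difference with its 95% CI at the end of each phase after randomisation.
- **Other continuous outcomes** (quality of life, social adjustment, cognition): the same approach wherever a score from before allocation exists.

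Use the same definition of baseline in Primary outcomes and in Sample size and randomization.

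The cost is analysis wording and one degree of freedom for the covariate. No added patients or visits are needed, since the covariate is a rating already recorded. For patients allocated after a relapse, that rating may be some time before allocation, because the article does not say that CGI-BP-M is rated at that point. The article describes the study as still in progress, so the change can be fixed in advance if it is made before outcome data are compared by arm.

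### The planned repeated-measures ANOVA relies on sphericity although the phase-end ratings are very unevenly spaced; a mixed model with its own contrast for each phase would be safer

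*Protocol article*

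**What the plan says.** All places are in the protocol article.

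- **Planned analyses**: "Continuous variables will be compared using repeated-measures of analysis of variance, with the treatment group and study phase as factors". No covariance structure, sphericity correction or error term for comparisons at a single phase is given. Group comparisons are two-sided at the 5% level.
- **Primary outcomes**: the outcome is "changes in mean scores on the CGI-BP-M between baseline and endpoint at the end of each phase of the study".
- **Sample size and randomization**: 25 patients per group, sized with a Student's t test on baseline-to-endpoint change, "for detecting a difference of 0.8 standard deviations, considered a large effect size", at 80% power.
- **Study phases**: phase I lasts 8 weeks, followed by "8 weeks in phase II (potentiation treatment) and shall continue in phase III (maintenance) until study endpoint at 2 years". That puts phase-end ratings at about weeks 8, 16 and 104.
- **Abstract (Methods/Design)**: phase II is 6 months and phase III is 12 months, which puts them at about weeks 8, 34 and 86.

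**The concern.** A t test on change uses the variance of that particular change. The classical repeated-measures ANOVA uses one within-patient error for everything that involves phase, which is valid when the difference between any two ratings has the same variance. Ratings 8 weeks apart will usually be more alike than ratings 88 weeks apart. If so, the common error is too small for the long interval and can be too large for the short one.

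At stake is the test that answers the trial's question. The group main effect is unaffected by non-sphericity, but it averages over the phases and does not test a difference in change. The group-by-phase test does, and it can reject too often. If comparisons at single phases borrowed the same error, a false difference in maintenance would become more likely and a real one at the end of phase II could be missed more often. Every other continuous outcome put through this model shares the problem.

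**Working it through.** **1. The plan's own figure.** For 0.8 SD, two-sided 5% and 80% power, the normal approximation gives n = 2(1.960 + 0.842)² / 0.8² = 24.5, so 25 per group (power 80.7%). The exact t test with 25 per group has power 79.1%. The stated sample size reproduces.

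**2. Rating times.** Study phases: 0, 8, 8 + 8 = 16, and 104 weeks. Abstract: 0, 8, 8 + 26 = 34, and 34 + 52 = 86 weeks.

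**3. Assumptions, none of them in the article.** SD 1 at each rating; correlation r^(gap/8 weeks) with r = 0.6 or 0.8; 25 complete patients per group; week 0 as baseline. Adding a constant patient component of 0.3 multiplies all the variances below by 0.7 and leaves their ratios unchanged.

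**4. Formulas.** The variance of change over a gap is V = 2(1 − correlation). The pooled error implies the same variance for every change, P = 2(1 − mean of the six pairwise correlations). Error df are 2 × 24 × 3 = 144, critical t 1.977. A pooled-error contrast at a phase then has approximately:

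- type I error = 2[1 − Φ(1.977 / √(V/P))]
- power for 0.8 SD of that change = Φ(0.8√(25/2) − 1.977 / √(V/P)), where 0.8√12.5 = 2.828

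Example (Study phases schedule, r = 0.8). The six correlations are 0.800, 0.640, 0.055, 0.800, 0.069 and 0.086, with mean 0.408, so P = 1.183. Phase III: V = 1.890, ratio 1.597, 1.977/1.264 = 1.564, error 11.8%. Phase II: V = 0.720, ratio 0.609, 1.977/0.780 = 2.534, power Φ(0.294) = 62%.

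| Weeks | r | P | V phase II | V phase III | Phase II power | Phase III type I error |
|---|---|---|---|---|---|---|
| 0/8/16/104 | 0.6 | 1.478 | 1.280 | 1.997 | 76% | 8.9% |
| 0/8/16/104 | 0.8 | 1.183 | 0.720 | 1.890 | 62% | 11.8% |
| 0/8/34/86 | 0.6 | 1.683 | 1.772 | 1.992 | 82% | 6.9% |
| 0/8/34/86 | 0.8 | 1.297 | 1.225 | 1.818 | 79% | 9.5% |
| 0/8/16/104 | 0.3 | 1.770 | 1.820 | 2.000 | 81% | 6.3% |

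**5. Simulation (at least 20,000 trials per setting, same assumptions).**

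- Overall group-by-phase F, uncorrected, under the null: about 6-8% on the Study phases schedule and about 5-7% on the Abstract schedule. The lower end of the second range arises when week 0 is left out.
- Pooled-error phase III contrast: about 9-13% and about 6-10% respectively, the second range again including runs without week 0.
- Each change tested with its own variance: about 5% throughout, with power about 79%.

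**6. Sensitivity.**

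- *Week 8 as baseline*, since allocation follows phase I. Study phases schedule: pooled phase III error about 8-10%, phase II power about 22-52%. Abstract schedule: phase II power about 68-76%.
- *Correlation 0.3 at 8 weeks, Study phases schedule*: overall F about 5%, phase III about 6-7%, phase II power about 81%. If the phase III SD is also 0.7, phase III falls to about 5%.
- *Correlation 0.6 with phase III SD 0.7, Study phases schedule*: phase III about 8%, phase II power about 80-82%. At correlation 0.8 the phase III inflation stays near 11%.
- *Constant correlation and equal SDs*: the data are spherical, and everything is at about 5% and 80%.

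**The case against.** The strongest objection is that the article names a family of analyses and not an error term. Greenhouse-Geisser or multivariate tests, and separate errors for single-phase contrasts, all fit its sentence, and such details commonly sit in a full protocol or analysis plan that is not shown. This stands against any claim that the plan uses a pooled error for phase contrasts. It does not remove the point that the stated method is a weaker match to a change-per-phase outcome than one readily available.

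Second, Planned analyses opens by describing the primary analysis as baseline against endpoint in the two groups. With only two ratings sphericity holds trivially, and the group-by-time F is the square of the t test used for sizing. That reading is possible. But the primary outcome refers to the end of each phase, and phase is named as a factor, so the multi-phase reading is at least as natural.

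Third, the simulated trial is simpler than the real one. Only responders enter phase III and non-responders after phase II leave, so phase III will be smaller, selected and perhaps less variable. This stands: the percentages illustrate a mechanism and are not estimates for this trial.

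A reader might infer that the plan tests phase III at 9-12% and forfeits its 80% power. The article does not support that. It states neither the pooled error nor any correlation or SD, its two schedules give different results, and the 80% belongs to a single t test for which it is correct.

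**Conclusion.** The concern holds in conditional form. A classical repeated-measures ANOVA over ratings this unevenly spaced relies on an assumption that the schedule makes doubtful. For the test the plan names, the likely excess is modest: about 6-8% in place of 5% on the Study phases schedule and about 5-7% on the Abstract schedule, given correlation of 0.6-0.8 at 8 weeks that decays, equal SDs and complete data. The larger figures need the further assumption that phase contrasts use the pooled error: about 9-13% (or 6-10%) for phase III, and phase II power of about 62-76% on the Study phases schedule. On the Abstract schedule there is little or no power loss if week 0 is the baseline. With weaker correlation or a smaller phase III SD the effect is smaller or absent. This is a worthwhile and cheap improvement to the analysis wording; it does not show that the planned result would be invalid.

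**What to change.** In Planned analyses, replace the repeated-measures ANOVA by a linear mixed model with unstructured covariance over the rating times and Kenward-Roger degrees of freedom. Report the lithium-aripiprazole contrast in CGI-BP-M change at each post-allocation phase end. Each contrast then has its own variance and corresponds to the t test used for sizing.

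If ANOVA is kept, state Greenhouse-Geisser corrected or multivariate tests for the overall effect, and each contrast's own error for single-phase comparisons. The Greenhouse-Geisser correction alone would not repair contrasts built on a pooled error.

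Reconcile the phase lengths in the Abstract and in Study phases, because the rating times depend on them. The sample-size statement needs no change on this account.

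The cost is a sentence or two of wording and a standard software option, with no new data. The downside is a few more variance parameters and slightly lower nominal power for the overall test: about 4-9 points with four ratings on the Abstract schedule, measured against an ANOVA test whose size is too large. The change does not deal with the selection of responders into phase III.
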